### **5.2. Participant and Study Completion**

As an initial target, up to 165 high risk participants per arm will be randomly assigned to study treatment or control in Brazil. There may be more than 165 patients randomized to the placebo arm during the entire duration of the trial given the possible addition of HCQ+LPV/r arm.

This sample size target will likely increase based on the blinded sample size re-assessment.

|                                          |                 |
|------------------------------------------|-----------------|
| Date/version: May 19, 2020 – V1.0 | Page: 24 |
|------------------------------------------|-----------------|

| Harmonized protocol document                                                          |
|---------------------------------------------------------------------------------------|
| Short title: Outpatient Management of SARS-CoV-2 for High-Risk Adults in LMICs |

A participant is considered to have completed the study if he/she has completed all phases of the study including the last scheduled procedure shown in the Schedule of Activities (SoA). The clinical evaluation of each experimental intervention will be considered completed when sufficient number of participants complete the study to enable appropriate evaluation of the primary endpoint.

| Harmonized protocol document                                                          |
|---------------------------------------------------------------------------------------|
| Short title: Outpatient Management of SARS-CoV-2 for High-Risk Adults in LMICs |

## 6. Study Population

Prospective approval of protocol deviations to recruitment and enrolment criteria, also known as protocol waivers or exemptions, is not permitted.

### 6.1. Eligibility criteria for Brazil

#### 6.1.1. Inclusion Criteria for Brazil

- Completed informed consent form
- Men and women 18 years of age or older with persistent dry cough associated with axillary temperature  $> 37.7^{\circ}\text{C}$ ; or recent onset of influenza associated with dry cough
- Laboratory confirmed SARS-CoV-2 infection, with test results within past 72 hours
- Possesses at least one of the following risk-factors for severe COVID-19 disease
  - Risk factors:
    1. Age  $\geq 50$  years
    2. Presence of pulmonary disease, specifically moderate or severe persistent asthma, chronic obstructive pulmonary disease (COPD), pulmonary hypertension, emphysema, or tuberculosis
    3. Diabetes mellitus (type 1 or type 2), requiring oral medication or insulin for treatment
    4. Hypertension, requiring at least 1 oral medication for treatment
    5. Known cardiovascular diseases (CHF of any etiology, documented Coronary Artery Disease, Miscellaneous heart disease with clinical repercussion)
    6. Symptomatic lung disease and / or being treated
    7. Patients with a history of transplantation
    8. Patient with stage IV chronic kidney disease or on dialysis.
    9. Immunocompromised status due to disease (e.g., those living with human immunodeficiency virus with a CD4 T-cell count of  $<200/\text{mm}^3$ , confirmed malignancy)
    10. Immunocompromised status due to medication (e.g., persons taking 20 mg or more of prednisone equivalents a day, anti-inflammatory monoclonal antibody therapies, or cancer therapies)
    11. Patients with cancer
    12. Body mass index  $\geq 30$  (self-reported or measured)
- Eligible patients must be willing to use the proposed investigational treatment and have ability to provide informed consent.

#### 6.1.2. Exclusion Criteria for Brazil

Participants are excluded from the study if any of the following criteria apply:

1. RT-PCR exam for SARS-CoV-2 negative during the screening visit
2. Known hypersensitivity to any of the study drugs

|                                          |                 |
|------------------------------------------|-----------------|
| Date/version: May 19, 2020 – V1.0 | Page: 26 |
|------------------------------------------|-----------------|

| Harmonized protocol document                                                          |
|---------------------------------------------------------------------------------------|
| Short title: Outpatient Management of SARS-CoV-2 for High-Risk Adults in LMICs |

3. Patients with an acute respiratory condition and with moderate to high probability of not being a SARS-CoV-2 infection
4. Currently hospitalized
5. Severe respiratory clinical condition, presenting at least ONE of the criteria below:
  - The respiratory rate > 28 / min;
  - SaO2 <90% with nasal oxygen therapy at 10 l / min;
  - PaO2 / FIO2 <300 mmHg
6. History of Cardiac Arrhythmia or Long QT Syndrome;
7. Use of Medications that are known to prolong QTc: Citalopran, Venlafaxina, Bupropion and with no possibility of suspension during the period of use of medications.
8. Inability to take oral medications;
9. Patients on continuous use of Amiodarone and / or PGE5 Inhibitors (Ex: Sildenafil and similar).
10. Use of Digoxin, Cyclosporine, Cimetidine, Tamoxifen
11. Use of anticonvulsants, antifungals, immunosuppressants other than corticotherapy.
12. Use of Hydroxychloroquine for other indications
13. Use of chemoprophylaxis for malaria.
14. Psoriasis in a form other than cutaneous
15. Porphyria
16. Use of protease inhibitors, ritonavir or Cobicistat
17. Clinical history of Liver Cirrhosis or Child-Pugh C classification;
18. Patients with a history of degenerative retinal diseases (patients with retinal diseases due to diabetes and hypertension may participate in the research);
19. Patient with a clinically relevant history of hearing loss;
20. Patients with known severe degenerative neurological diseases and / or severe mental illness;
21. Inability of the patient or representative to give consent or adhere to the procedures proposed in the protocol;
22. Taking chronic medications associated with prolonged QT and may induce Torsades de Pointes as per CredibleMeds.org, including certain antipsychotic medications or antidepressants (e.g., citalopram, venlafaxine, and bupropion) and unable to stop during the trial
23. Baseline QTc interval of > 470 ms in males, and > 480 ms in females
24. Potentially clinically significant pharmacokinetic and pharmacodynamic drug interactions as determined by the study clinical pharmacologist\*\*
25. Pregnancy or lactating women

Note:

\*Patients who have already started on the assigned therapy may stop treatment if they test negative for SARS-COV-2 during screening

\*\* If randomization to one study arm may be considered to put the patient at increased risk due to drug interactions, randomization will be limited to the arms with safer interventions. This is important to allow participation of HIV-infected participants on treatment and rifampicin-treated participants.

|                                          |                 |
|------------------------------------------|-----------------|
| Date/version: May 19, 2020 – V1.0 | Page: 27 |
|------------------------------------------|-----------------|

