### **5.1.1. Study Execution for Brazil**

This study will be carried in two stages: *Internal Pilot and Main Stages*

Due to the rapid evolution of the COVID-19 pandemic and the challenge that public health systems will face to respond to this devastating infection, there are several aspects related to the feasibility of the study that need to be evaluated as soon as we start implementing it.

The aim of the internal pilot phase is to assess any unpredictable feasibility problems and resolve them to improve the overall success of the research. In particular, we will assess issues related to drug recruitment, consent, availability and administration, data collection and recording. This will involve about 18-20 patients in total. There will be no statistical analysis at the end of the pilot stage. The pilot and main stages will be operationally connected with the patients enrolled in the pilot stage will be transferred to the main stage during which the recruitment efforts will be amplified.

The pilot stage will start with two arms: HCQ and placebo, with LPV/r possibly being added if the drug supply becomes available during the pilot stage.

The main stage will begin with three arms: HCQ, LPV/r, and placebo. Safety profile of the monotherapy arms will be tested after being administered for 100 patients per arm. This will be reviewed internally and externally with AbbVie. If adequate safety profile is observed in both monotherapies, combined arm of HCQ + LPV/r will be added into the TOGETHER 2 with permission from AbbVie.

With the time required to review the safety profile of HCQ and LPV/r monotherapy with AbbVie, (assuming adequate safety profile) the fourth arm of combined HCQ + LPV/r will likely be introduced into the trial after enrolment of 165 per arm has already been randomized to the three initial groups of placebo, HCQ, and LPV/r.

For the clinical evaluation of HCQ + LPV/r arm versus placebo, we will use unequal allocation of 3:1 (165 for combined arm and additional 55 for placebo arm) and will incorporate the previously placebo control data by borrowing the individual treatment effects of HCQ and LPV/r versus placebo as empirical prior for the clinical evaluation of the combined arm.

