#### **Sensitivity analysis:**

The primary analyses will be repeated replacing randomization arm by actual treatment to account for possible off-label use of and noncompliance to the investigational products.

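### Exclusion 12 bars hydroxychloroquine only for indications other than COVID-19, so no named criterion covers a patient already taking it for COVID-19

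*Protocol*

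**What the plan says.** Protocol 6.1.2 treats the two study drugs differently. Exclusion 12 is "Use of Hydroxychloroquine for other indications". Exclusion 16 is "Use of protease inhibitors, ritonavir or Cobicistat", with no reference to indication.

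Two later criteria could touch a patient already on HCQ:
- Exclusion 22 begins "Taking chronic medications associated with prolonged QT and may induce Torsades de Pointes as per CredibleMeds.org" and applies only if the patient cannot stop the drug during the trial.
- Exclusion 24 is "Potentially clinically significant pharmacokinetic and pharmacodynamic drug interactions as determined by the study clinical pharmacologist". Its footnote adds that, where one arm would put a patient at increased risk, "randomization will be limited to the arms with safer interventions". Section 3.3 repeats this.

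Section 5.1.1 holds back the combination. It says "Safety profile of the monotherapy arms will be tested after being administered for 100 patients per arm", and then "If adequate safety profile is observed in both monotherapies, combined arm of HCQ + LPV/r will be added into the TOGETHER 2", subject to the manufacturer's permission.

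The protocol expects non-study use of the drugs. The sensitivity analysis in 12.3.1 replaces randomised arm by actual treatment "to account for possible off-label use of and noncompliance to the investigational products". Section 7.8 records concomitant medication but, in the text shown, restricts none of it. Section 8.1 names prohibited concomitant medication as a reason to stop study treatment, without a list in the text shown. The Day 0 list in 10.1.1 gives placebo patients the standard treatment chosen by the treating team.

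**The concern.** COVID-19 is the trial's own indication, so a bar on HCQ for other indications leaves HCQ for COVID-19 untouched. Such patients are plausible on the protocol's own terms. Section 6.1.1 accepts a positive test up to 72 hours old, and note 1 to the Schedule of Activities provides for patients whose positive result is already known at screening, so there is time to have been prescribed treatment.

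Three things are at stake:
- A placebo patient on HCQ is not an untreated control for HCQ, and an HCQ-arm patient already on the drug does not start it at randomisation. The HCQ comparison shrinks.
- An LPV/r patient on HCQ takes both drugs, possibly before the review in 5.1.1, and that patient's adverse events count as LPV/r monotherapy data.
- The planned sensitivity analysis cannot repair this. Regrouping by treatment actually taken gives up the randomised comparison.

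**Working it through.** **Does any other criterion close the gap?**

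| Exclusion | What it covers | Names HCQ taken for COVID-19? |
|---|---|---|
| 7 | Three named antidepressants | No |
| 12 | HCQ for other indications | No, by its qualifier |
| 13 | Malaria chemoprophylaxis | No |
| 16 | Protease inhibitors, ritonavir, cobicistat | No |
| 22 | Chronic QT-prolonging drugs, if the patient cannot stop | No; a short new course is not clearly chronic |
| 23 | Baseline QTc threshold | No |
| 24 and footnote | Interactions, as judged by the study pharmacologist | No; discretionary |

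No named criterion covers the patient.

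**Inputs.** From 12.1: control event rate 20%, RRR 27.5%, 492 per arm, two-sided 5% error, 90% power. The event rate on HCQ is therefore 0.20 × (1 − 0.275) = 0.145. Assumption: a share p of placebo patients takes HCQ with its full effect, and earlier HCQ adds nothing further in the HCQ arm. The documents do not give p.

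**The plan's own figure.** The usual two-proportion formula with pooled variance under the null,

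n = [1.960·√(2·p̄(1−p̄)) + 1.282·√(p₁(1−p₁) + p₂(1−p₂))]² / (p₁−p₂)²,

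with p₁ = 0.20, p₂ = 0.145 and p̄ = 0.1725, gives 990 per arm, not 492. At 492 per arm the power is 62.7%. That mismatch is a separate matter. It is noted here because it sets the starting power, so both sizes are shown.

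**HCQ versus placebo.** Observed placebo rate = 0.20 × (1 − 0.275p). Apparent RRR = 1 − 0.145 / observed placebo rate.

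| p | Placebo rate | Apparent RRR | Power, 492 per arm | Power, 990 per arm |
|---|---|---|---|---|
| 0 | 0.2000 | 27.5% | 62.7% | 90.0% |
| 10% | 0.1945 | 25.4% | 54.3% | 83.5% |
| 20% | 0.1890 | 23.3% | 45.6% | 74.7% |
| 40% | 0.1780 | 18.5% | 29.0% | 51.4% |

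**LPV/r versus placebo.** Randomisation spreads HCQ use at entry evenly over these arms. If the two drugs' effects multiply, both rates are scaled by (1 − 0.275p) and the RRR stays at 27.5%. Taking that as LPV/r's true effect, power at 492 per arm is 62.7%, 61.3%, 59.8% and 56.8% for p = 0, 10%, 20% and 40%. The small loss comes from fewer events.

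**Safety review.** If the share on HCQ among the first 100 LPV/r patients were 10%, 20% or 40%, then 10, 20 or 40 of them would be on both drugs, unless exclusion 24 or its footnote is used.

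**The case against.** The strongest objection is exclusion 24 with its footnote. Section 7.2.1 says the regimens may prolong QT, so HCQ with LPV/r is the kind of pair this review exists for, and the pharmacologist may exclude the patient or limit the arms. A reader might infer from exclusion 12 that pre-treated patients can enter any arm and that the gate in 5.1.1 is bypassed. The documents do not support that. Exposure to both drugs is possible only if the discretion is not used, and 5.1.1 governs the opening of a randomised combination arm, not background medication. What remains is that the review depends on individual judgement, does not name HCQ, and concerns interactions. It therefore gives no reason to exclude a patient bound for placebo.

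A reader might also infer that both active comparisons are damaged alike. They are not. For LPV/r the cost is a changed background treatment and mixed safety data, with little loss of power.

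Nor does the Day 0 list in 10.1.1 show that medication is recorded too late. It is an unordered list, note 7 to the Schedule of Activities requires all criteria to be settled before randomisation, and the Schedule places concomitant medication at screening.

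Three further limits stand:
- The values of p have no source in the protocol.
- Full effect is generous for someone who began HCQ shortly before entry.
- The intervention appendices, not shown, may restrict non-study HCQ.

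**Conclusion.** The gap in the wording is real. Exclusion 12 leaves out HCQ taken for COVID-19, no other named criterion covers it, and the text shown gives no reason for the difference from exclusion 16.

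The main consequence is dilution of HCQ versus placebo. The bias is toward the null, so the risk is a missed effect, not a false positive. With a 20% control rate, a true 27.5% RRR and full effect in pre-treated placebo patients, the apparent RRR is 25.4% at p = 10% and 18.5% at p = 40%. These figures illustrate the mechanism and do not predict its size.

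The second consequence is conditional: some LPV/r patients may take both drugs before the review in 5.1.1 if exclusion 24 and its footnote are not applied, which would mix the monotherapy safety data.

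Confidence is moderate, because the appendices are not shown.

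**What to change.** Delete the qualifier in exclusion 12, so that it reads in parallel with exclusion 16. Alternatively, state in 6.1.2 whether non-study HCQ for COVID-19 is allowed at entry, and reconcile that statement with exclusions 16 and 24 and with the review in 5.1.1. Have HCQ use checked from the concomitant medication record that the Schedule of Activities places at screening, before randomisation.

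Rewording exclusion 12 deals only with use at entry. HCQ begun afterwards would dilute the comparison in the same way, so the recoverable loss is only the part due to entry. Sections 7.8 (recorded, not restricted), 8.1 (prohibited medication without a list in the text shown) and 10.1.1 (standard treatment for placebo patients) must be reconciled with each other. Which clinical rule to adopt is for the sponsor.

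The cost is a one-line amendment to 6.1.2 plus the cross-checks. A few pre-treated patients become ineligible, and recruitment is slightly slower.

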| Patient Identification Card                                                                  |                                                  | X                                                   |                               |                              |                               |                              |                               |                               |                               |                               |                                                        |

1. Baseline visit may be performed at the same time as the screening visit. For patients without RT-PCR results, quick test for COVID-19 at the screening visit and randomization will be done after confirmation of SARS-CoV-2 infection. For patients with known RT-PCR positive results, screening and baseline visit will be done on the same day.
2. Visits made through telephone contact, calculated in relation to the randomization date. Home visits will be made for mid-nasal or saliva collection.

3. Only women of childbearing potential and / or potential to become pregnant. Urine pregnancy test for women with at least one menstruation in the last 12 months
4. After signing the Informed Consent Form.
5. Scales and questionnaires must be completed BEFORE any procedures of the proposed visit and must be self-applied. Only a person not related to the research can help the patient during the filling. In telephone visits, the patient must respond directly, at the time of contact.
6. Remind the patient that they will answer the questionnaire.
7. After completing the screening / baseline visit procedures and presenting all inclusion / exclusion criteria, patients should be immediately randomized.
8. The study medication will be administered as prescribed.
9. The first treatment dose under investigation must be administered on the same day of randomization (immediately after randomizing)
10. Maintain the administration of the product under investigation according to schedule. Patients administration to study drug as per protocol assessed. Discontinuation if adverse events prevent the medication from continuing.
11. Medication adherence will be assessed on Day 10 over the phone or in person.
12. As soon as the patient start the product under investigation.
13. Verification of clinical outcomes (e.g. symptoms, hospitalization and etc) will be done via telephone. On days when home visits are made, verifications of clinical outcomes may be done in person.

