| 
 
To test the efficacy of experimental interventions to prevent progression to LRTI, among persons with SARS-CoV-2 infection who are at high risk of progression
 
To test the efficacy of experimental interventions to reduce SARS-CoV-2 viral shedding
 
 | 
 
LRTI, defined by SpO2<93% or decline from baseline of 6% in 2 measurements at least 2 hours apart. Initially, the trial is statistically powered for this endpoint in high-risk population.
 
Proportion of persons with clearance of SARS-CoV-2 from nasal swabs or saliva, defined as 1 negative swab
 
 |
| 
 
To test the safety and adherence of experimental interventions for treatment of high-risk outpatients with SARS-CoV-2 infection
 
                                                                                                                                | 
 
Serious adverse events (including death, hospitalization) and adverse events resulting in treatment discontinuation up to 28 days
 
Proportion of non-adherent patients with interventions
 
                                                                                                                                   |
| 
 
To test whether any of the experimental interventions has an effect on hospitalization and mortality among persons who become hospitalized with COVID-19 disease (continued from primary outcome)
 
                                                              | 
 
Proportion hospitalized for COVID-19 progression
 
Days of hospitalization
 
Mortality for any causes after randomization up to 90 days
 
Mortality due to pulmonary complications
 
Mortality due to cardiovascular complications
 
                                                                      |

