## **6.2. Screen Failures**

Screen failures are defined as participants who consent to participate in the clinical study but are not subsequently randomly assigned to study treatment. A minimal set of screen failure information is required to ensure transparent reporting of screen failure participants to meet the Consolidated Standards of Reporting Trials publishing requirements and to respond to queries from regulatory authorities. Minimal information includes demography, screen failure details, eligibility criteria, and any serious adverse event (SAE).

Individuals who do not meet the criteria for participation in this study (screen failure) can be rescreened if there is a change in their eligibility.

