#### **The participant will do the following on Day 0:**

- Interactive Web Response System (IWRS) registration and randomization after PCR confirmation (the expected turn around for PCR testing is 12-24 hours)
- Recheck the inclusion / exclusion criteria and verify the participant's interest in continuing in the study
- Physical examination, including weight, height, vital signs measurement (seated/supine PA, pulse rate, and temperature)
- Collection of concomitant medication information
- Delivery of medications and guidelines for the assigned medications
- Delivery of medicines under investigation. The patient will receive the drugs under investigation as allocated by IWRS (patients in the placebo group will receive the standard treatment defined by the assistant team) and the necessary instructions for use.

- Patient will receive a card with 24-hour telephone contact to call if necessary. Patient will be guided on daily telephone contact and on the collection kits for viral load research.
- Take study therapy (as assigned)
- Tolerance towards the assigned therapy
- Confirmation of adherence to study therapy dosing
- Daily dosing time
- Reporting of adverse events
- Cardiac measurement using Kardiamobile monitors
- SpO2, respiratory rate, temperature and pulse measurements
- Measurement of heart rate (pulse oximeter) at rest after the participant remained seated at rest for 5 minutes
- Blood pressure measurement after the participant was seated at rest for 5 minutes
- Clinical symptoms review
- WURSS-11 survey for dyspnea
- Tisdale scale
- EQ-5D-5L
- Guidance on daily telephone contacts
- COVID-19 guidelines and quarantine recommendations

Eligible participants will be randomized. Participants will be instructed how to self-assess respiratory rate. Local health care providers wearing personal protective equipment will deliver and collect study related mid-nasal swabs and DBS cards as needed.

Participants will be assessed at the home visits during the mid-nasal swab or saliva collection thermometer, Kardiamobile device, and pulse oximetry device.

The SARS-CoV-2 positive test results will be confirmed through laboratory records.

Patients tested negative for COVID-19 will be considered a screening failure, and only positive patients will be treated and invited for subsequent follow-ups.

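### The protocol contradicts itself on whether assigned therapy can start before a negative SARS-CoV-2 result, leaves follow-up of such a patient unclear, and counts baseline-negative patients as cleared

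*Protocol*

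**What the plan says.** **Order of test, randomisation and dose.** Section 6.1.1 requires "Laboratory confirmed SARS-CoV-2 infection, with test results within past 72 hours". Exclusion 1 in Section 6.1.2 is "RT-PCR exam for SARS-CoV-2 negative during the screening visit". Footnote 1 to the schedule in Section 2.1 provides, for patients without an RT-PCR result, a "quick test for COVID-19 at the screening visit and randomization will be done after confirmation of SARS-CoV-2 infection". The Day 0 list in Section 10.1.1 has "registration and randomization after PCR confirmation", with an expected PCR turnaround of 12-24 hours. Footnote 9 of Section 2.1 puts the first dose immediately after randomisation.

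The note at the end of Section 6.1.2 describes a different situation: "Patients who have already started on the assigned therapy may stop treatment if they test negative for SARS-COV-2 during screening".

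**What happens to a negative patient.** Section 10.1.1 says "Patients tested negative for COVID-19 will be considered a screening failure, and only positive patients will be treated and invited for subsequent follow-ups". Section 6.2 defines screen failures as "participants who consent to participate in the clinical study but are not subsequently randomly assigned to study treatment". Section 9 keeps participants who stop study product in the study, with evaluations continuing on schedule. Section 12.2 puts everyone randomised in the ITT population.

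**Clearance endpoint.** The Synopsis and Section 4.1 give it as "Proportion of persons with clearance of SARS-CoV-2 from nasal swabs or saliva, defined as 1 negative swab". Section 12.3.2 assesses all secondary endpoints in the ITT population.

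**The concern.** Therapy that has been assigned has been randomised. The note therefore presupposes that randomisation and dosing came before a negative screening result, which the main sequence rules out.

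If such a patient occurs, the sections point in different directions. Section 10.1.1 would end treatment and follow-up. Sections 6.2, 9 and 12.2 would keep the patient in follow-up and in the analysis. If sites resolve this differently, or resolve it knowing the treatment, outcomes go missing after randomisation. Section 7.5 concedes that full blinding of patients and treating clinicians is not feasible, so that loss need not be balanced between arms.

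The clearance endpoint is a second and independent problem. A patient with no detectable virus at baseline cannot clear it, yet one negative swab scores as success. That raises the rate in every arm and pulls the difference towards zero.

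**Working it through.** **1. Can the note's patient arise?** No arithmetic applies, so the provisions are set side by side.

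| Provision | Place | Implication for a patient dosed and then found negative |
|---|---|---|
| Randomise only after confirmation | 2.1 footnote 1; 10.1.1 | Should not exist |
| Negative RT-PCR at screening excluded | 6.1.2, exclusion 1 | Should not have been enrolled |
| Already on assigned therapy, may stop | 6.1.2, note | Exists; stopping is optional |
| Negatives are screening failures; only positives treated and followed | 10.1.1 | No follow-up |
| Screen failure means never randomised | 6.2 | Cannot be a screen failure |
| Those who stop product continue evaluations | 9 | Followed |
| All randomised are ITT | 12.2 | Analysed |

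The protocol's own pathway allows the case. For a known RT-PCR positive, footnote 1 puts screening and baseline on the same day, and the first dose follows randomisation at once. The schedule also takes a study sample at screening for confirmation and viral load. With a 12-24 hour turnaround, that sample can be read after the first dose. The qualifying outside result may be up to 72 hours old.

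**2. Size of the clearance effect.** The documents give neither the baseline-negative share f nor any clearance rates. Assumed for illustration: 50% (control) and 65% (active) among baseline-positive patients, and every baseline-negative patient meeting the one-negative-swab rule.

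Observed rate = f + (1-f) × true rate, so observed difference = (1-f) × true difference.

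| f | Control | Active | Difference (points) |
|---|---|---|---|
| 0% | 50.0% | 65.0% | 15.0 |
| 1% | 50.5% | 65.35% | 14.85 |
| 5% | 52.5% | 66.75% | 14.25 |
| 10% | 55.0% | 68.5% | 13.5 |
| 20% | 60.0% | 72.0% | 12.0 |

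**3. Hospitalisation.** Inputs from Section 12.1: 492 per arm, control event rate 20%, relative risk reduction 27.5%, two-sided 0.05. The treated rate is 0.20 × (1 - 0.275) = 14.5%. The endpoint is hospitalisation or worsening for COVID-19, so assume that uninfected patients have no events. At f = 10%:

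- control 0.9 × 20% = 18%; treated 0.9 × 14.5% = 13.05%
- relative reduction 1 - 13.05/18 = 27.5%, unchanged
- absolute difference falls from 5.5 to 4.95 points

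Power by the pooled two-proportion formula is Φ{[√n·|p1-p2| - 1.96·√(2p̄(1-p̄))] / √(p1(1-p1)+p2(1-p2))}. At n = 492 per arm it goes from 62.7% (f = 0) to 62.2% (f = 1%) and 57.3% (f = 10%). If those patients' outcomes are lost instead, it is 62.3% and 58.2%. The starting value is not the stated 90%; that is a separate matter, and only the change is relevant here.

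**4. Is the baseline sample fixed before treatment?** The schedule in Section 2.1 labels it D0 but marks it under Screening. Section 10.1.1 has it on Day minus 1. The shedding objective in Section 4.1 and Section 11.1.1 start at Day 1. The first dose falls on the day of randomisation, D-0, so a Day 1 sample would come after it.

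**The case against.** The strongest reply is that this is one stray note. Its asterisk has no visible anchor in the exclusion list, though exclusion 1 is the likely place. Every other passage requires confirmed infection, and read in its own sequence Section 10.1.1 speaks of patients not yet randomised, which agrees with Section 6.2. Section 9 already keeps patients who stop product in follow-up, and Section 12.2 already puts them in the ITT. Much of this stands. A reader might infer that the plan directs sites to drop randomised patients or removes them from the ITT. The documents do not support that: the loss needs a site to apply a screening rule to a randomised patient. But Section 10.1.1 does not limit its rule to the time before randomisation, and an ITT definition does not supply outcomes that were never collected.

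A reader might also infer that the planned 27.5% relative reduction in hospitalisation is diluted. That needs uninfected patients to be hospitalised for COVID-19 at the control rate, which is implausible. With no such events the relative reduction is unchanged.

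Nor is a patient with an outside positive within 72 hours uninfected because a later study sample is negative. That patient meets the inclusion criterion and belongs in the clinical analysis. The difficulty is confined to the virological endpoints.

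Finally, the clearance denominator might be called detail for the SAP, to which Section 12.2 defers a fuller description of populations. But the protocol itself states both the success rule and the ITT denominator, and together they give the wrong count. The effect applies equally to all arms on average, so it attenuates the difference and does not create a false one.

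**Conclusion.** The contradiction is in the text and needs no outside figure: the note in Section 6.1.2 cannot stand with Sections 2.1 and 10.1.1, and Section 10.1.1 as worded conflicts with Sections 6.2, 9 and 12.2 for any patient the note describes. The consequence is a possible loss of outcomes on randomised participants, not a certain one. The documents do not show how many patients would be affected.

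The clearance rule counts baseline-negative patients as successes. The difference shrinks by (1-f): 0.15 points at f = 1% and 1.5 points at f = 10%, for an assumed true difference of 15 points. The effect on the hospitalisation comparison is small when f is small, and there is none on the relative reduction if uninfected patients have no COVID-19 events.

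This should be corrected, but it falls short of a defect that must be resolved before the trial can be relied on.

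**What to change.** 1. Reconcile footnote 1 of Section 2.1, Section 6.1.2 (exclusion 1 and the note), Section 6.2, Section 9 and Section 10.1.1 into one sequence of confirmation, randomisation and first dose. Which treatment rule applies is for the sponsor and the investigators; this review does not choose it.
2. State in Section 10.1.1 that screening failure applies only before randomisation, and that every randomised patient is followed as in Section 9 and analysed as in Section 12.2, whatever a later test shows.
3. Define viral clearance and change in viral load in participants who are PCR-positive on the baseline study sample. State that this sample is taken before the first dose, and align its timing across Sections 2.1, 4.1, 10.1.1 and 11.1.1. Without that condition the subset is not guaranteed to be fixed before treatment.

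The cost is wording. No new samples are needed. A few baseline-negative patients leave the virological denominator and remain in the ITT for the clinical endpoints.
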